### Sampling procedure

Multistage, stratified and systematic sampling will be used to recruit study participants from the facilities where they attend. Using data available from the 2010 Population and Housing Census, three out of the formerly ten regions in Ghana with adolescent pregnancy rates higher than the national average (14%) were randomly selected. Subsequently, six districts were purposefully selected from these regions considering appropriateness for the intervention, available resources, and geographical non-proximity between intervention and control facilities. Facilities in the intervention and control arms of the study were matched based on the number of adolescent pregnancies delivered annually using the Ghana Health Service District Health Information Management System (GHS-DHIMS) data from 2018 as a guide.

All eligible adolescent participants who attend the participating intervention and control facilities for antenatal care in their third trimester and delivery will be invited to enrol in the study by a trained research assistant. The nature of the study and all ethical concerns will be explained to the candidate prior to their enrolment. Enrolment will be run on a cumulative bases until the minimum sample size is satisfied. Some adolescents will be purposively selected to participate in the adolescent IDIs based on their characteristics which is aimed at achieving maximum variability of participants. Each district will have a health professional who works in administrative capacity and in a caregiving capacity invited to participate in the Key Informant Interviews.

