## Methods

### Study settings

The study intervention will be sited in three regions in Ghana: Eastern, Central and Greater-Accra regions. The intervention sites are public health facilities in the Lower Manya Krobo, Upper Manya Krobo district, and the Awutu-Senya East Municipality. The control sites will be in the Ada East, Shai-Osudoku and Effutu Districts. These districts have an average of 11% of their population being adolescent females [42] and reported adolescent pregnancy rates higher than the national average of 14% [22] . The intervention and control sites are selected health facilities which are matched on the type of facilities being district health centres and district hospitals. For each of the intervention sites, a senior member of the district quality of care team will be included as a resource person in the RMC trainings.

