### Data collection procedure

The quantitative interviews will be administered by trained research assistants. Interviews will be administered both at baseline and endline (from day 1 following the intervention). They are estimated to last between 30 and 45 min per participant and will be held at the home of the participant or a convenient private venue outside the health facility within two weeks after delivery. This venue arrangement is considered important to create an enabling environment which allows free and candid dialogue with the participant which may not be possible at the health facility due to fear of retaliation from providers. This time interval between delivery and the interview is also considered adequate for the parturient to recuperate without introducing significant recall bias. Interviews with adolescent participants will be in the most commonly spoken languages in the district which are English, Twi, Dangme or Krobo, based on the preference of the participant. This will allow the participants to express themselves freely in the language they are most comfortable with.

Qualitative IDIs will be conducted with selected adolescent participants and KIIs with health professionals. Interviews will be audio-taped, with prior permission from the participant. Additionally, notes will be taken to capture non-verbal nuances and expressions which may aid in better analysis and interpretation of the audio information. The number of interviews will continue until a saturation of information is reached. Each interview is estimated to last between 45 and 60 min. For adolescents, IDIs will take place at a location convenient to the participant outside the facility within two weeks after delivery. Similar to the quantitative interviews, the qualitative interviews will be conducted within a post-recovery timeframe which mitigates the probability of recall bias. Based on the preference of the participant, IDIs will be conducted in English, Twi, Ga-Dangme or Krobo as done in the quantitative interviews. The KIIs will be conducted within the facilities where the staff work and will be conducted in English.

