### Data processing and statistical analysis

Both baseline and endline data will be reviewed and edited for completeness and consistency daily. The primary outcome variable of interest is defined as disrespectful intrapartum care which is measured as a response of “Yes” to any of the nine mistreatment questions. The explanatory variables of interest include socio-economic status, educational level, marital status and knowledge of health rights. Data will be collected on the KoBoCollect platform, synced onto a web server and downloaded in Ms-Excel format to the principal investigator’s computer. The data will be exported in STATA version 16 for cleaning and analyses. Descriptive statistics as well as binary and multiple logistic regressions will be computed. Additionally, Difference in Differences (DID) will be calculated to determine the net RMC training intervention effect on mistreatment and RMC. Finally, statistical significance of the RMC training intervention effect will be evaluated using adjusted prevalence ratio, adjusted odds/risk ratio at 95% confidence interval (CI) and *P*-Value of less than 0.05.

Audiotapes from qualitative interviews will be translated and transcribed verbatim into Ms-Word format in English. Themes will be identified and coded in Ms-Excel and exported into NVivo for analyses. Quotes will be narrated and cited in participant codes.

Data analysis for qualitative and quantitative data will be conducted separately. Subsequently, inferences from both qualitative and quantitative results will be jointly used to draw conclusions.

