### Limitations

There are a few limitations in this study which measures have been taken to address. Firstly, it was not possible to randomly assign the study sites due to geographical and health system constraints. It is therefore possible that there will be observed and unobserved differences in the baseline measures of the intervention and comparison groups that may account for differences in outcomes. However, the study sites were selected based on their similarities in characteristics such as type of facility and socio-geographic factors. Furthermore, the use of difference-in-differences analytic methods in the analyses of data will allow the account of both observed and unobserved confounders. Another limitation that may be faced is the employment of new staff into intervention facilities after the intervention has been conducted. To mitigate this limitation, we shall take note of new staff and encourage the training module to be shared during their staff orientation.

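### The difference-in-differences names no facility term, so a change in facility mix that differs between arms could bias it in either direction; facility indicators are a cheap safeguard

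*Protocol article*

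**What the plan says.** **Allocation and matching.** The Sampling procedure section of the protocol article states that "six districts were purposefully selected from these regions considering appropriateness for the intervention, available resources, and geographical non-proximity between intervention and control facilities". It adds: "Facilities in the intervention and control arms of the study were matched based on the number of adolescent pregnancies delivered annually". Study settings describes the facilities as "matched on the type of facilities being district health centres and district hospitals". The data quality assurance section repeats similarity of facilities as the basis for allocation.

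**Who is surveyed.** Women are interviewed within two weeks of giving birth. Baseline collection lasts three months, and endline collection runs from the day after the intervention to three months after it. The two waves are therefore in effect different women. Eligible attenders are invited cumulatively until the minimum sample is reached. No number per facility or per wave is given. Sampling is called stratified, but the stratifying variable is not named.

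**Analysis.** The statistical analysis section says: "Descriptive statistics as well as binary and multiple logistic regressions will be computed" and "Difference in Differences (DID) will be calculated to determine the net RMC training intervention effect on mistreatment and RMC". On covariates it says: "The explanatory variables of interest include socio-economic status, educational level, marital status and knowledge of health rights". Facility, facility type, district and matched set are not mentioned, although the questionnaire collects facility factors and the sample size allows for clustering.

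**What DID is said to achieve.** Limitations states that "the use of difference-in-differences analytic methods in the analyses of data will allow the account of both observed and unobserved confounders".

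**The concern.** With repeated cross-sections, a DID of pooled arm-by-wave proportions compares averages over whichever facilities supplied the women in each wave. A stable difference between two facilities is a time-constant confounder at facility level. It does not drop out of the pooled average if the weights on those facilities move. A change in where adolescents were enrolled can then appear as a change in how they were treated.

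This is separate from the effect of clustering on standard errors. Cluster-robust errors would widen the interval but leave the point estimate where it was.

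The Limitations sentence makes this more than an unstated detail. It offers DID as the answer to non-random allocation and does not say that only time-constant differences are removed, or that facility composition must be held fixed or modelled for facility differences to cancel.

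**Working it through.** The protocol gives no figure for facility mix or facility-specific rates, so there is none to reproduce. The check has three parts.

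**Inputs from the protocol (Sample size determination; total also in the Abstract):** baseline mistreatment 18%, planned reduction 10 points (to 8%), design effect 1.11, total 392.

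**Assumptions:** facility rates, enrolment shares and shifts; three to ten facilities per arm (three would be one per named district); 392 split equally over two arms and two waves, 392 / 4 = 98 per cell.

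**1. Mechanism, with a true training effect of zero.** Take two facilities per arm and a linear model.

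- *Shift in the intervention arm only.* Rates are 28% and 8% in both arms. The intervention share from the high-rate facility falls from 50% to 30%. Baseline mean: 0.5 × 28 + 0.5 × 8 = 18. Endline mean: 0.3 × 28 + 0.7 × 8 = 14. Control stays at 18. DID = (14 − 18) − (18 − 18) = −4.0 points.
- *Same shift in both arms, equal gaps.* DID = (14 − 18) − (14 − 18) = 0.
- *Same shift in both arms, unequal gaps.* Control rates are 20.5% and 15.5%, so control moves from 18 to 0.3 × 20.5 + 0.7 × 15.5 = 17. DID = (14 − 18) − (17 − 18) = −3.0 points.

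DID in points under three models:

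| Scenario | No term | Matched-set term | Facility term |
|---|---|---|---|
| Intervention arm shifts to low-rate facility, equal gaps | −4.0 | 0.0 | 0.0 |
| Intervention arm shifts to high-rate facility, equal gaps | +4.0 | 0.0 | 0.0 |
| Same shift in both arms, equal gaps | 0.0 | 0.0 | 0.0 |
| Same shift in both arms, unequal gaps | −3.0 | −3.0 | 0.0 |
| Intervention arm only, unequal gaps | −4.0 | −1.6 | 0.0 |

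Only the facility term gives zero throughout. The 20-point gap is chosen to show the mechanism and is not an estimate.

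**2. Plausible size.** With equal gaps in both arms, bias = rate gap × differential change in share. To see what gap the protocol's own design effect allows, use ICC = (1.11 − 1) / (m − 1), with m women per facility and wave, and between-facility SD = √(ICC × 0.18 × 0.82).

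- Three facilities per arm: m = 98 / 3 = 32.7, ICC = 0.0035, SD = 2.3 points.
- Ten facilities per arm: m = 9.8, ICC = 0.0125, SD = 4.3 points.

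A gap of 4.5 points is about two SDs in the first case and about one in the second.

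| Rate gap | Shift 10 | Shift 20 | Shift 30 |
|---|---|---|---|
| 4.5 points | 0.45 | 0.9 | 1.35 |
| 10 points | 1.0 | 2.0 | 3.0 |

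Rates of 26% and 10% with a 20-point shift give 16 × 0.20 = 3.2 points. A 16-point gap is 16 / 4.3 = 3.7 SDs even in the ten-facility case, so it presumes more variation than the design effect implies.

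**3. Against sampling error.** With 98 per cell, SE of the DID = √[(3 × 0.18 × 0.82 + 0.08 × 0.92) / 98] = 0.073, or 7.3 points (before any design effect). A bias of 0.9 is about 0.12 SE, and 3.2 is about 0.44 SE.

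**The case against.** The strongest reply is that this is a condensed article. It gives no model equation for the DID. The covariate sentence is open-ended, is not tied to the DID, and could equally describe the risk-factor regressions. A reader might infer that the trial will fit no facility term and that its estimate will be biased. The text supports neither inference: not naming a term does not show that none will be fitted. That part of the objection stands.

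Three further points also stand. Stratified sampling could hold the mix steady if the stratum is the facility, though this is not stated. Inviting every eligible attender at the same facilities over similar periods would tend to make shares follow delivery volume, and the documents give no reason to expect a large differential shift. A shift in mix is also not sufficient for bias, since equal shifts with equal facility gaps cancel.

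It would also be too strong to say that the analysis throws the matching away. Matching on type and volume still makes the arms more alike by design. It does not guarantee equal mistreatment rates between matched facilities.

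What the objection does not reach is the Limitations sentence. A fuller analysis plan could add a facility term, but the published claim for DID would remain too broad.

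**Conclusion.** The point holds as a cheap improvement to the stated analysis, not as a demonstrated bias. The named analysis does not by itself protect against a non-cancelling change in facility mix, and the protocol's account of what DID controls is wrong as written.

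Bias requires that facilities differ in mistreatment rate and that their enrolment shares change differently between arms, or change equally where facility gaps differ between arms. A reader might infer that the error would always flatter the training. It would not: the direction depends on which facilities gain or lose share.

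The size cannot be determined from the documents. About 1 point is plausible under the 1.11 design effect with assumed facility numbers and shifts, and about 3 points under larger assumed gaps and shifts. That is roughly a tenth to a third of the planned 10-point effect and less than half of the DID standard error. More extreme assumptions give more, but nothing in the protocol supports them.

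**What to change.** In the statistical analysis section, specify the DID with an indicator for each facility, an indicator for wave and the arm-by-wave term. The facility indicators absorb the arm main effect, and each facility is then compared with itself over time. A matched-set or facility-type term should not be used as a substitute, because it can leave the whole bias when facility gaps differ between arms.

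In Limitations, restrict the statement about DID to confounding that is constant over time. Facility indicators will not remove changes within a facility that coincide with the training.

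The cost is one model line and one sentence. Facility must be recorded for each woman; the article does not say so explicitly, but recruitment takes place at the facilities. The model uses a few degrees of freedom. Facilities with very few women or no events can cause estimation problems in a logistic model and may need grouping, or a linear-probability model may be used instead.

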### Measurement tools

Quantitative data will be collected with the aid of an electronically-based structured questionnaire adapted from Bohren and colleagues’ study [44] which has been modified to suit the local context. The tool is designed to collect data on the socio-demographic characteristics of adolescents and their knowledge on health and sexual reproductive rights. The tool will additionally collect data on the labour experience including the provider-patient encounter and relationships, encounters of mistreatment and RMC, and health facility factors.

Qualitative data collection will be done with the aid of interview guides adapted from the studies by Bohren et al. [44] and Afulani and colleagues [45]. The tool is specifically developed to collect data on the varying forms of mistreatment within the local context. Sections of the guide probe for an in-depth discussion on the themes of knowledge on health and sexual reproductive rights, provider-patient interactions, encounters of mistreatment and RMC and health facility factors. For professionals, the interview will probe for the role of healthcare providers in the labour experience especially in the administration of RMC.

### Data collection procedure

The quantitative interviews will be administered by trained research assistants. Interviews will be administered both at baseline and endline (from day 1 following the intervention). They are estimated to last between 30 and 45 min per participant and will be held at the home of the participant or a convenient private venue outside the health facility within two weeks after delivery. This venue arrangement is considered important to create an enabling environment which allows free and candid dialogue with the participant which may not be possible at the health facility due to fear of retaliation from providers. This time interval between delivery and the interview is also considered adequate for the parturient to recuperate without introducing significant recall bias. Interviews with adolescent participants will be in the most commonly spoken languages in the district which are English, Twi, Dangme or Krobo, based on the preference of the participant. This will allow the participants to express themselves freely in the language they are most comfortable with.

Qualitative IDIs will be conducted with selected adolescent participants and KIIs with health professionals. Interviews will be audio-taped, with prior permission from the participant. Additionally, notes will be taken to capture non-verbal nuances and expressions which may aid in better analysis and interpretation of the audio information. The number of interviews will continue until a saturation of information is reached. Each interview is estimated to last between 45 and 60 min. For adolescents, IDIs will take place at a location convenient to the participant outside the facility within two weeks after delivery. Similar to the quantitative interviews, the qualitative interviews will be conducted within a post-recovery timeframe which mitigates the probability of recall bias. Based on the preference of the participant, IDIs will be conducted in English, Twi, Ga-Dangme or Krobo as done in the quantitative interviews. The KIIs will be conducted within the facilities where the staff work and will be conducted in English.

### Data quality assurance activities

The quality of the study and data collected will be assured via the following means
Intervention-Control Allocation: The intervention and control facilities are selected based on the similarity of their characteristics. This includes the type of facility, proportion of adolescent deliveries per year and the socio-demographic characteristics of the community. The geographic non-proximity of the facilities was also highly considered to avoid contamination of the control communities.Research Assistants Recruitment, Training & Monitoring: Research assistants will be selected based on the following criteria
Sex: femaleAge: 18 to 25 yearsAcademic qualification: minimum of a secondary school certificateTechnical proficiency: smartphone literacyLanguage proficiency: at least one of the languages (Ga-Dangme/ Krobo/Twi)The age group and sex of the assistants will help establish rapport between the assistants and participants. This will also help minimize response desirability bias on the side of participants. The educational and technical criterion are necessary to ensure that the assistants understand and effectively carry out their roles in the study to collect quality data. The assistants will undergo a two-day training on the theoretical background of the study, enrolment and obtaining consent from participants, administration of questionnaires and facilitation of interviews, as well as ethical issues. The principal investigator will always closely supervise the research assistants to ensure their observance of study protocols and ethical codesData Collection Instruments: The data collection instruments are adapted from a previous multi-country study (which included Ghana) which included parturient women of all ages [46] instruments will be adapted for use with adolescents. The tools will be pretested on 5% of the sample size in a pilot facility in the Kpone-Katamanso district and modified accordingly based on findings from the pilot. The pilot district was selected based on its similarity to study sites in having an adolescent birth rate of greater than 11%.Data Collection Timing and Location: Data collection at baseline will be over a 3-month period. Endline data collection will start from day 1 after the intervention until three-months post-intervention. The venue and time interval between delivery and the adolescent surveys will allow participants express themselves freely without fear of victimization by health providers. This will also allow the participants enough recovery time from childbirth with minimal recall bias.Data Monitoring: Data collection will be conducted in real time electronically. The data will be monitored daily to allow early detection of discrepancies and resultant remedial action. Transcripts from audio interviews will be reviewed by an independent listener who is fluent in the language and did not conduct or transcribe the interview to audit for accuracy and completeness.

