### Intervention

The proposed intervention aims to educate and inform midwives about the concepts of mistreatment and RMC. The training additionally seeks to help participants explore and shift their current values and beliefs about mistreatment of adolescent parturients towards more positive behaviours. It also aims to encourage the practice of RMC by promoting adherence to positive professional codes of conduct, ethics, roles, values and attitudes. The proposed intervention is a training module facilitated with the aid of a resource package adapted from the White Ribbon Alliance/ USAID “Respectful Maternity Care for Healthcare Workers: Tackling Disrespect & Abuse During Facility-Based Childbirth” project [47]. Additionally, the structure and content of the module is influenced by evidence from previous studies and systematic reviews on mistreatment and RMC [48–54]. This course will be presented in the format of presentations, case studies, role plays, discussions and evaluations. The content will cover the adolescent and their reproductive health rights, the Ghana Health Service (GHS) code of professional ethics, Nurses and Midwives Code of Conduct, definitions and typologies of mistreatment and RMC as well as their outcomes to the woman, neonate, professional and health system. The content will also cover the professionals’ role in the delivery of RMC. The training workshops will be implemented by the principal investigator supported by a facilitator who is member of the District Quality of Care team. Each workshop will be a two-day event. The first day will cover a theoretical introduction of the concepts of mistreatment and RMC and the role of the obstetric professional. The second day will be a series of case studies and role plays to apply the theoretical basis from day 1. The facilities will additionally be provided with visible posters and materials as a constant reminder of the contents of the training programme.

There will be no intervention conducted in the control facilities.

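### The investigator who delivers the training also closely supervises the interviewers who collect the self-reported primary outcome, and no stated safeguard deals with knowledge of arm

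*Protocol article*

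**What the plan says.** Intervention gives delivery of the training to the principal investigator: "The training workshops will be implemented by the principal investigator supported by a facilitator who is member of the District Quality of Care team". It also provides posters and materials in the trained facilities and no intervention in the control facilities.

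Data collection procedure assigns outcome measurement to the assistants: "The quantitative interviews will be administered by trained research assistants". Data quality assurance activities puts them under the same principal investigator, "The principal investigator will always closely supervise the research assistants to ensure their observance of study protocols", and describes what they are taught: "The assistants will undergo a two-day training on the theoretical background of the study". Under Sampling procedure, eligible adolescents attending intervention and control facilities "will be invited to enrol in the study by a trained research assistant".

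Data processing and statistical analysis defines the endpoint: "The primary outcome variable of interest is defined as disrespectful intrapartum care which is measured as a response of" yes to any one of nine mistreatment questions. On handling, it says "Both baseline and endline data will be reviewed and edited for completeness and consistency daily", without naming who edits, and that the data are synced to a web server and then "downloaded in Ms-Excel format to the principal investigator", that is, to that person's computer.

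The stated protections for the survey are a structured electronic questionnaire, a venue away from the facility, young female interviewers and daily monitoring. The one independent check is a second listener for the audio transcripts, which belong to the qualitative part.

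**The concern.** The endpoint depends on what a participant says to an interviewer, and a single yes among nine items decides her classification. The people closest to that answer are likely to be able to tell a trained facility from an untrained one. They have been taught the thinking behind the study, and they work under the person who ran the training. How firmly a question is put, how a hesitant answer is recorded, or how a discrepancy is resolved during daily review could then differ by arm.

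The article's protections concern the participant's fear of providers and her wish to please. They are the same in both arms and do not deal with the expectations of an arm-aware interviewer, supervisor or editor. Limitations names non-random sites and new staff, and relies on difference-in-differences for observed and unobserved confounding. It does not mention unmasked outcome assessment. At stake is whether a change in recorded mistreatment can be read as a change in care rather than partly a change in measurement.

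**Working it through.** **1. Roles, set side by side**

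| Task | Who | Section |
|---|---|---|
| Delivers training | Principal investigator, with a district facilitator | Intervention |
| Supervises interviewers | Principal investigator | Data quality assurance activities |
| Elicits the primary outcome | Research assistants | Data collection procedure |
| Enrols participants attending the facilities | A research assistant | Sampling procedure |
| Edits survey data daily | Not named | Data processing and statistical analysis |
| Receives the downloaded data | Principal investigator | Data processing and statistical analysis |
| Independent check | Audio transcripts only | Data quality assurance activities |

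The overlap between training and supervising is stated outright. That recruiting assistants will know the arm is an inference from on-site enrolment and the posters; it is likely but not stated.

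**2. What difference-in-differences removes**

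Let D = (trained endline − trained baseline) − (control endline − control baseline), using recorded rates. Assume the true rate is 18% in all four cells (the sample-size section's prevalence) with no true effect. Let one or more cells record only 90% of true yes answers: 18% × 0.90 = 16.2%. The 90% is an assumption; the article gives no such rate.

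- Both arms, endline: (16.2 − 18) − (16.2 − 18) = 0. Removed.
- Trained arm, both waves: (16.2 − 16.2) − (18 − 18) = 0. Removed.
- Trained arm, endline only: (16.2 − 18) − (18 − 18) = −1.8 points. Kept, as a false benefit.
- Control arm, endline only: (18 − 18) − (16.2 − 18) = +1.8 points. Kept, as a false harm.
- Trained arm, baseline only: (18 − 16.2) − (18 − 18) = +1.8 points. Kept, as a false harm.

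The method removes measurement error that is stable within an arm or common to a wave. It keeps error specific to one arm in one wave, and the sign depends on which cell is affected.

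**3. Size in the trained-arm, endline scenario**

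- 90% elicited: 1.8 points, and 1.8/10 = 18% of the planned 10-point reduction.
- 80% elicited: 18% × 0.80 = 14.4%, so 3.6 points, and 3.6/10 = 36% of the planned reduction.

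**4. Effect on false positives**

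Take the stated total of 392, allow for 10% non-response and the design effect of 1.11: 392 × 0.9 / 1.11 ≈ 318 effective participants. Use an unpooled two-sided 5% z-test with a true effect of zero.

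- Endline comparison of two groups of about 159: rejection in about 7% of trials at 90% elicitation and 14% at 80%.
- Four cells of about 79 each, testing D: about 6% and 7%.

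The main harm is therefore a distorted estimate that cannot be told apart from a training effect. With the sample split over four cells, false positives rise only a little.

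**The case against.** The strongest reply has four parts.

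- **Silence is not absence.** This is a condensed article, and masking or interviewer assignment may be set out in a fuller protocol. That stands as a caution: the text does not say that interviewers are told the allocation. It does not undo the stated overlap of training and supervision.
- **The questionnaire is structured.** Yes/no items in an electronic form leave less room for interviewer influence than an open interview. This reduces the concern but does not remove it, because the article does not say the items must be read verbatim, and assistants still explain and record.
- **The enroller may not be the interviewer.** Correct: the article does not say that the assistant who recruits a woman also interviews her at home.
- **The elicitation rates are invented.** Correct, and they are labelled as assumptions.

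Three stronger readings are tempting and not supported. A reader might infer that control facilities have no study contact, so that any bias acts only on the trained arm at endline. In fact assistants enrol in both arms, both arms are surveyed at both waves, and professionals in every district are invited to interview. A reader might infer that the principal investigator personally edits the outcome data. The article names no editor, and the stated purpose is completeness and consistency. A reader might also infer that the bias must favour the training, but the calculation shows that the sign depends on which cell is affected.

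**Conclusion.** The point holds in a limited form. The protocol places training delivery and close supervision of outcome collection in the same hands, teaches interviewers the study's theory, has enrolment done where the arm is likely to be visible, and describes no protection against arm-aware elicitation or editing of a self-reported endpoint. Difference-in-differences would not remove a measurement difference that arises in one arm after training.

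Direction and size are unknown. The 1.8 to 3.6 points rest on an assumed 10% to 20% under-elicitation in the trained arm at endline, a true rate of 18% in all cells and no training effect. They show scale and are not a forecast. This does not invalidate the design. It is a weakness in interpretation that can be reduced cheaply before data collection.

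**What to change.** With the existing staff:

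1. In Data quality assurance activities, replace the theory component for survey interviewers with verbatim, scripted administration of the nine questions. Do not tell them the hypothesis or which facilities are trained.
2. In Data processing and statistical analysis, lock the raw server export. Make the daily completeness and consistency edits on a copy in which arm and facility names are replaced by neutral codes. Log every edit, and freeze the file before arm codes are merged.
3. Where feasible, do not have an assistant interview women she recruited on site.
4. In Limitations, state that the trainer supervises outcome collection and that masking is at best partial. This matters because steps 1 to 3 leave supervision where it is.

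The cost is a revised interviewer script, an assignment list, a coded export and an edit log. The intervention and sample size do not change. Masking will remain incomplete, because posters and local knowledge can reveal the arm, and consistency checks become slightly harder without facility names.

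Two further measures are not asked for. Having each assistant interview in both arms would be a real burden, since the sites were chosen to be far apart and an assistant needs only one local language. Hiding the survey wave from a daily review would not work, because baseline and endline are separate calendar periods.
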